#### Brief intervention

Participants will receive the GHS Program Information Booklet by email or mail and are offered a one-off coaching call with a health coach for information and advice on these topics to supplement the written material [32]. These participants will also have the option to enrol in the 6-month coaching program at any point.

### Data collection procedures and measures

The primary outcomes of the trial include behaviour change outcomes: (1) minutes of moderate to vigorous physical activity conducted per week, (2) average serves of fruit consumed per day over the past month, (3) average serves of vegetables consumed per day over the past month, as well as a composite dichotomous outcome of (4) whether participants attempted to change any of the following health behaviours or biomedical risk factors over the past six months: increase physical activity, fruit consumption, vegetable consumption, any other dietary changes, weight, or alcohol consumption. Secondary outcomes for biometric risk factor change will include (1) self-reported weight (kg) and (2) body mass index (BMI). Secondary outcomes will also include dichotomous outcomes of attempts to change behaviours or biomedical risk factors individual, including (1) physical activity, (2) fruit consumption, (3) vegetable consumption, (4) other parts of their diet, (5) weight, or (6) alcohol consumption in the last 6 months.

Data to assess primary and secondary outcomes, plus some additional variables listed below (see also Fig. 2), will be collected using CATI surveys by telephone interviewers experienced with working with mental health clients. The surveys will take approximately 30 min. During the interview, participants will be asked if they have the visual aid for serving sizes available. Those with the visual aid will be asked to refer to it throughout the survey; however, verbal explanations of these serving sizes based on Australian guidelines [35, 37] will be provided to all participants. Follow-up surveys will be completed using the same method approximately six months post-recruitment.

**Fig. 2 Fig2:**
[figure not shown]
SPIRIT figure schedule of enrolment, intervention, and assessments

Data will also be obtained from the intervention service provider in the form of monthly reports on relevant contact variables for intervention group participants (see process outcomes below). The trial management team will attempt to contact any intervention participants who cease the intervention by passive withdrawal (do not graduate or terminate coaching but are unable to be contacted for a routine coaching call). Two attempts to contact the participant by telephone will be made. If the participant is successfully contacted, the trial management team will request permission to re-refer the participant to the GHS, who will reattempt to contact the participant and recommence the coaching program.

### Primary and secondary outcomes

The outcome and additional variables included in the survey will be as follows (at both baseline and follow-up unless stated otherwise):

#### Physical activity

The Simple Physical Activity Questionnaire (SIMPAQ) will be used to measure minutes of moderate to vigorous physical activity conducted per week. The SIMPAQ is a five-item self-report measure of physical activity over the past seven days which includes reported time spent in bed, sedentary and napping time, minutes of walking, minutes of physical activity, and minutes of other incidental activity [38]. Moderate-vigorous physical activity (MVPA) is calculated using the self-reported time in physical activity, time spent walking, and time spent exercising per week. The measure has been validated for people with a mental health condition [38]. The alternative SIMPAQ method for calculating sedentary time will be used, outlined by Rosenbaum et al., subtracting the total reported time spent on all activities from 24 h and confirming the remaining total with the participant as an accurate reflection of sedentary time per day [38].

#### Fruit and vegetable consumption

Participants will be asked to respond to single-item questions to identify the number of serves of fruit and vegetables consumed daily: e.g. “over the past month… how many serves of fruit do you eat in a usual day?” (number of serves/do not know). These items have been used in previous studies with a mental health population [39]. Participants with the visual aid available will be prompted to refer to the image guides for standard serving sizes of fruit and vegetables.

#### Attempts to change health behaviours

Six items will be used to record self-reported attempts to reduce health behaviours over the past 4 months, including “In the last four months, have you attempted to…”: increase physical activity, fruit consumption, or vegetable consumption; make any other changes to diet or nutrition; lose weight; reduce alcohol consumption (for participants that reported consuming any alcohol) (yes/no/do not know).

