#### Coaching program

Participants will receive a copy of the GHS Program Information Booklet, which consists of an evidence-based information package about healthy eating, physical activity, and weight management in accordance with the Australian Guide to Healthy Eating [35] and the National Physical Activity Guidelines [36], and a journey booklet, which includes tracking tools and support tips to utilise throughout their coaching program. Coaching participants will complete an initial registration call to discuss their current eating and activity behaviours, determine their readiness to make changes, and set their personalised healthy lifestyle goals. They will then be allocated to a university-qualified health coach (such as a dietician, physiotherapist, or exercise physiologist) based on their identified goals. The service provides evidence-based support using motivational interviewing and self-regulation principles to develop motivation, overcome barriers, and sustain lifestyle changes including healthy eating, physical activity, healthy weight management, and alcohol reduction [32]. The coaching program consists of up to 13 proactive, individually tailored coaching calls with their health coach over six months to assist participants in setting healthy lifestyle goals and to provide educational material and support to achieve and maintain their lifestyle changes [32]. Specialised versions of the program exist for participants who are pregnant, identify as Aboriginal and/or Torres Strait Islander origin, are identified as being at risk of type-II diabetes, or have a primary goal of reducing alcohol consumption. Calls are tapered throughout the program, with more frequent calls during the first 12 weeks to assist with initiating behaviour change and less frequent calls during the second half of the program to support change maintenance [32]. Participants can stop the coaching program at any time, either by withdrawal if they have not achieved their health goal or as an ‘early graduation’ if they achieve their health goal in less than 13 calls and choose not to complete the remaining coaching calls. If participants wish to withdraw from the trial, they may advise their health coach, who will contact the trial management team, or contact the trial management team directly.

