#### Sample size and power

The study will aim to recruit 675 participants (540 intervention and 135 control following the 4:1 allocation ratio). As per the intention-to-treat analysis, 55% of participants are anticipated to provide follow-up data (*n* = 297 intervention, *n* = 75 control, total 372). This final sample will provide an 80% power to detect a true difference between groups at follow-up of 0.58 serves of vegetables per day (SD = 1.6) [47], 0.47 serves of fruit per day (SD = 1.3) [35], and 109 min of moderate/vigorous physical activity per week (SD = 300) [48].

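### Primary outcome 4 and the individual attempt outcomes are defined over six months, but the survey items are described as asking about four months; the windows must be reconciled for baseline and follow-up

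*Protocol article*

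**What the plan says.** In the Protocol article, Data collection procedures and measures, primary outcome 4 is a dichotomous composite: "whether participants attempted to change any of the following health behaviours or biomedical risk factors over the past six months". The same paragraph lists the six individual attempts as secondary outcomes and closes the list with the same window: "5) weight, or (6) alcohol consumption in the last 6 months".

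The section Attempts to change health behaviours describes the only instrument given for these outcomes: "Six items will be used to record self-reported attempts to reduce health behaviours over the past 4 months". It then gives the item itself, which begins "In the last four months, have you attempted to".

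On timing: "Follow-up surveys will be completed using the same method approximately six months post-recruitment". On the intervention, the Coaching program section says: "The coaching program consists of up to 13 proactive, individually tailored coaching calls with their health coach over six months". Calls are tapered, "with more frequent calls during the first 12 weeks to assist with initiating behaviour change".

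Two other places bear on the remedy. Primary and secondary outcomes says the survey variables are collected at both baseline and follow-up unless stated otherwise. Statistical analysis models the attempt outcomes with group, time and their interaction.

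**The concern.** The definition and the instrument disagree by two months for one of four primary outcomes and for six secondary outcomes. This is not a detail left to an analysis plan. The article states both windows, and an analysis plan cannot recover attempts that interviewers did not ask about.

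With a follow-up interview at about six months, a six-month window covers the whole period since recruitment, while a four-month window leaves out its first third. An attempt is an act of starting, and the programme concentrates its calls early to help people start. Someone who tried and stopped within the first two months is an attempter under one section and a non-attempter under the other. While both stand, the window could be settled after the data are seen, or four-month data could be reported as six-month data.

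**Working it through.** The article gives no expected attempt rate and no power for primary outcome 4, so there is no stated figure to reproduce. The check is a comparison of the two sections followed by date arithmetic.

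**1. The windows side by side**

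| Place in the Protocol article | Window |
|---|---|
| Data collection procedures and measures, primary outcome 4 | 6 months |
| Data collection procedures and measures, individual attempts | 6 months |
| Attempts to change health behaviours, description | 4 months |
| Attempts to change health behaviours, item wording | 4 months |

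Each window appears twice, once in words and once as a numeral, so a single slipped digit is an unlikely explanation.

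**2. Uncovered time, if the four-month item is asked at six months**

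- Recruitment to follow-up: 6 months = 26.09 weeks.
- Recall: 26.09 × 4/6 = 17.39 weeks.
- Uncovered: 26.09 − 17.39 = 8.70 weeks, which is 2/6 = 33% of the period.

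**3. Overlap with the denser coaching phase**

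The 12 weeks of more frequent calls are weeks of the coaching programme, not weeks since recruitment. Let L be the lag in weeks from recruitment to the start of coaching. The share of the 12 weeks that falls in the uncovered window is (8.70 − L)/12, and zero once L exceeds 8.70. The article does not give L, so the values below are assumptions.

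- L = 0: 8.70/12 = 72%
- L = 2: 6.70/12 = 56%
- L = 4: 4.70/12 = 39%

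L = 0 is an upper bound. An online referral, a call from the service, a decision to enrol, a registration call and allocation of a coach all come first (Intervention condition; Coaching program).

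**4. Who changes category**

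Only a participant whose attempts all fall in the uncovered window is classified differently. For the composite, an attempt on any listed item that continues, recurs or is new in months 2 to 6 still counts.

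**5. Effect on the group difference**

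Let e be the proportion of an arm whose attempts are all confined to the first two months. With accurate recall and an interview at exactly six months:

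six-month difference = four-month difference + (e in intervention − e in control).

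The article gives neither value of e, so both the size and the sign of the bracket are unknown. It is positive if referral mainly prompts brief early attempts. It is negative if coaching keeps people trying while control participants try early and stop.

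**The case against.** The strongest reply is that this may be only a drafting slip. The interview script is not shown, and if it asks about six months at both surveys, the measures section is misreported and one line corrects it. That is fair: the documents establish a contradiction, not which window is wrong. The correction is needed either way, because a reader cannot tell what was asked.

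The second reply is that little would be lost even with the four-month item. Coaching runs over six months, and the composite counts an attempt on any of several behaviours. About half of the intervention arm is expected not to enrol (Statistical analysis), so those participants have no dense phase to miss. This stands as a limit on the consequences.

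A third reply is that both arms are mailed the same health information pack, so early attempts prompted by the pack drop out of both. A longer window on a composite of this kind could also push both arms towards a ceiling and shrink the difference. A four-month window at six months lies wholly after randomisation, so it still gives a fair comparison, though of a different outcome. All of this stands. A reader might infer that the four-month item dilutes the treatment contrast, but without attempt rates the documents do not support that.

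**Conclusion.** The inconsistency is real. Primary outcome 4 and the six individual attempt outcomes carry a six-month window in one section and a four-month window in another, and nothing in the article resolves it. It must be corrected because it sits in the definition of a primary outcome.

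The coverage loss is conditional. If the four-month wording is used at a six-month follow-up, attempts confined to about the first 8.7 of 26 weeks are missed. The overlap with the early coaching calls depends on the lag to the first call: at most 72% of the 12-week phase, and 39% with an assumed four-week lag.

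Two stronger readings go beyond the documents. One is that no attempt begun in the first two months is captured; attempts that persist or recur later are. The other is that the instrument certainly cannot deliver the outcome; that holds only if the four-month wording is the one fielded. Randomisation and the stated power, which concerns the three continuous outcomes, are unaffected.

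**What to change.** - Make the two sections agree, and state the window actually asked at baseline and at follow-up.
- For follow-ups still to be done, use a window covering the whole post-randomisation period: six months, or since the first interview. Anchoring to the interview date also copes with follow-up at only approximately six months, when a fixed six-month recall could reach back before randomisation.
- State the baseline window as well. The items are asked at both surveys and modelled with a group-by-time interaction, so if the windows differ in length, the time effect mixes real change with window length and must be interpreted accordingly.
- Where the four-month wording has already been used, define and report the outcome as attempts in the past four months, and record the item version for each interview.

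The cost is a change to the interview script and a sentence in the outcome definition. The downside is two item versions if some follow-ups are already complete, which is possible because recruitment began in October 2019 (Trial status). If the script already asks about six months at both surveys, only the measures section needs correcting.

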#### Biometrics

Height (cm or feet/inches) will be collected at baseline and self-reported weight (kg, pounds, or stone) in both baseline and follow-up surveys. These will be used to calculate a BMI score (kg/m^2^) [40].

### Additional measures

#### Alcohol consumption

Alcohol consumption will be measured using the short form of the Alcohol Use Disorders Identification Test (AUDIT-C) [41, 42]. Alcohol consumption is not a primary outcome as it is not the main focus of the GHS for most participants, with less than 1% of clients selecting an alcohol-reduction goal [29]; however, it has been included to measure any possible effects to other health risk behaviours addressed.

#### Participant characteristics

*Sociodemographic*: demographic information collected at baseline will include age, gender identity, highest level of education, current employment status, current marital status, and Aboriginal and/or Torres Strait Islander status. *Clinical*: primary and any secondary mental health diagnoses for which the participant is currently receiving or has received treatment for within the past 12 months and any physical health conditions that have required treatment within the past 2 months. These questions will be included in the baseline survey only. Current medications for mental health conditions will be recorded during baseline and follow-up surveys. *Health behaviour risk status*: calculated as per the Australian Guidelines for each health behaviour, with risk defined as follows; tobacco smoking, e.g. “how often did you smoke tobacco products in the last month?” (any use of tobacco products), and from the measures outlined above for alcohol consumption (AUDIT-C) [41, 42], physical activity (SIMPAQ) (< 150 min/week of MVPA) [36], and fruit (< 2 serves daily) and vegetable consumption (< 5 serves) [35].

#### Interest and confidence to change health behaviours

Participants will be asked to rate (i) their interest in making changes and (ii) their confidence in making changes to each of the six health behaviours. The ratings will be made on a Likert-type scale (1 to 10) where one represents ‘not at all interested/confident’ and 10 represents ‘extremely interested/confident’.

#### Psychological wellbeing

The six-item Kessler-6 (K6) [43] measure will be used to measure psychological wellbeing.

#### Quality of life

The 12-item Australian Quality of Life (AQoL-4D) [44, 45] has been validated for an Australian mental health population and will be used to measure quality of life.

#### Process measures

Process outcomes data provided by the GHS will include: whether contact has been made with the participant, enrolment in GHS, program selection (brief intervention, coaching), number of coaching calls, total call duration, and program completion status. Intervention participants will be advised that process data will also be provided by the GHS. Intervention participants will also be asked at follow-up about their experience with the service. Those who enrolled will be asked about program satisfaction, coaching and service delivery. Acceptability and appropriateness of the intervention will be assessed using the short 4-item versions of the Acceptability of intervention Measure and the Intervention Appropriateness Measure [46].

### Data management

All client data shared with the trial management team and GHS will be shared via secure data transfer link. No clinical information will be provided by the mental health services. Contact details will only be used to contact mental health service clients and potential participants about the study and confirm interest in participating. Details of clients who opt-out of contact will be removed. All participants are allocated a unique identification number and will be advised as part of the verbal consent process that their contact details will be released only to the trial management team and the GHS for intervention participants. All data will be stored in a REDCap database on a secure server held on site at the University of Newcastle and will only be accessed by ethics-approved researchers on the project and statisticians assisting with data analyses.

#### Auditing

Due to the nature of the intervention, the GHS will audit the intervention conduct as per their internal service procedures. Process data supplied by the GHS will also be used by researchers to monitor intervention conduct.

### Statistical analysis

Descriptive statistics will be used to describe baseline participant characteristics by group. Analyses will follow intention to treat principles, where participants are analysed according to their randomised treatment allocation. The initial analyses will be undertaken using all participants who provided baseline data. The three primary outcomes that are continuous variables (minutes physical activity, fruit serves, vegetable serves) will be analysed using linear mixed models, including a random intercept and random time effect for participant, as well as fixed effects for treatment group, time, and group*time interaction, and possible confounding variables including age, gender identity, and mental health diagnosis. Similar analyses will be conducted for continuous secondary outcomes (weight, BMI).

The same analyses using logistic mixed models will be conducted for dichotomous primary and secondary outcomes (attempts to change health behaviour variables).

As it is expected that approximately 50% of intervention participants will not enrol with the GHS (Fig. 1), an exploratory ‘per protocol’ analysis will be undertaken based on only those intervention participants who enrolled with the GHS (enrollers analysis). There are no interim analyses planned.

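### The mixed model for the continuous primary outcomes estimates a baseline difference that randomisation makes zero; this wastes precision, and the contrast behind the stated 80% power is not tied to the model

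*Protocol article*

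**What the plan says.** In the protocol article, Statistical analysis, the three continuous primary outcomes (activity minutes, fruit serves, vegetable serves) are analysed by linear mixed models on everyone with baseline data. The models have a random intercept and a random time effect for participant, "as well as fixed effects for treatment group, time, and group*time interaction", and covariates such as age, gender identity and diagnosis. Weight and BMI are handled similarly. No coefficient or contrast is named as the treatment effect.

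Sample size and power plans for "675 participants (540 intervention and 135 control following the 4:1 allocation ratio") and expects that "55% of participants are anticipated to provide follow-up data", giving 297 and 75. It then states: "This final sample will provide an 80% power to detect a true difference between groups at follow-up", with differences of "0.58 serves of vegetables per day (SD = 1.6"), "0.47 serves of fruit per day (SD = 1.3") and "109 min of moderate/vigorous physical activity per week (SD = 300"). No baseline to follow-up correlation is given.

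The Randomisation section has interviewers trigger allocation once the baseline survey is finished.

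**The concern.** The power statement concerns a difference at one time point. The model has a separate baseline mean for each arm, and its usual headline coefficient, group by time, is the difference in change between arms. These are different quantities with different variances, and nothing in the protocol links the stated 80% to a term in the model.

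The free baseline difference also has a price of its own. Allocation comes after the baseline survey, so the true baseline difference is zero. With 540 and 135 participants the estimated difference still has a standard error of √(1/540 + 1/135) = 0.096 SD, which is about 0.15 vegetable serves per day (0.096 × 1.6) or 29 minutes of activity per week (0.096 × 300). The 4:1 allocation makes the control arm the main source of that noise. Part of it passes into the treatment effect whichever contrast is read from the model. At stake is avoidable loss of precision on three of the four primary outcomes and, on one reading, power below what is stated.

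**Working it through.** **Inputs.** From Sample size and power: randomised N = 540 and 135; followed up n = 297 and 75 (55%); SDs 1.6, 1.3 and 300; differences 0.58, 0.47 and 109. Assumed, because the protocol does not state them: two-sided alpha of 0.05; correlation r between baseline and follow-up, shown over a range; equal SD at both times; follow-up missing at random; no gain from the other covariates.

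**Step 1: reproduce the stated figure.** The detectable difference for an unadjusted two-sample comparison is (1.960 + 0.842) × SD × √(1/297 + 1/75), where the square root is 0.1292.
- Vegetables: 2.8016 × 1.6 × 0.1292 = 0.579 (stated 0.58)
- Fruit: 2.8016 × 1.3 × 0.1292 = 0.471 (stated 0.47)
- Activity: 2.8016 × 300 × 0.1292 = 108.6 (stated 109)

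At the stated differences the power is 80.1%, 79.9% and 80.3%. The stated calculation is therefore a raw follow-up comparison that uses no baseline information.

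**Step 2: variance of each contrast.** With baseline on all N and follow-up on n in each arm, in units of SD² and summed over arms:
- Interaction (difference in change): (1-r²)/n + (1-r)²/N
- Follow-up contrast from the same model (group + group by time): (1-r²)/n + r²/N
- Follow-up contrast with a common baseline mean: (1-r²)/n

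Dividing by 1/297 + 1/75 and using n/N = 0.55 gives the variance relative to the stated calculation:
- Interaction: (1-r²) + 0.55(1-r)² = (1-r)(1.55 + 0.45r)
- Follow-up contrast, free baseline: (1-r²) + 0.55r² = 1 - 0.45r²
- Common baseline: 1-r²

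The cost of the free baseline difference is thus 0.55(1-r)² on the first reading and 0.55r² on the second. Both are positive for every r strictly between 0 and 1.

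**Step 3: power for vegetables**, as Φ(0.58 / (1.6 × √variance) - 1.96). The other two outcomes agree to within 0.3 percentage points. Powers use the exact counts.

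| r | Interaction: rel. variance | power | Follow-up, free baseline: rel. variance | power | Common baseline: rel. variance | power |
|---|---|---|---|---|---|---|
| 0 | 1.55 | 61.4% | 1.00 | 80.1% | 1.00 | 80.1% |
| 0.2 | 1.31 | 68.7% | 0.98 | 80.8% | 0.96 | 81.7% |
| 0.3 | 1.18 | 73.3% | 0.96 | 81.7% | 0.91 | 83.7% |
| 0.4 | 1.04 | 78.6% | 0.93 | 82.9% | 0.84 | 86.4% |
| 0.5 | 0.89 | 84.5% | 0.89 | 84.5% | 0.75 | 90.0% |
| 0.6 | 0.73 | 90.8% | 0.84 | 86.5% | 0.64 | 93.9% |

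**Step 4: break-even for the interaction.** Setting (1-r)(1.55 + 0.45r) = 1 gives 0.45r² + 1.10r - 0.55 = 0, so r = (-1.10 + √2.20)/0.90 = 0.426. With the exact counts it is 0.427. Below this the interaction has less power than stated; above it, more.

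**The case against.** The strongest reply is that the protocol never says the interaction is the test. It lists model terms, and the only comparison it names is the difference at follow-up, in Sample size and power. That difference can be estimated from the same model as group plus group by time, and its relative variance, 1 - 0.45r², never exceeds 1, so the stated 80% is kept. Choosing the contrast is also commonly left to an analysis plan, which is not shown here. The model as written is unbiased under randomisation.

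Most of this stands. A reader might infer that the planned test misses 80% power. The documents do not support that: it needs both a test that the protocol does not name, though it is the common one for this model, and a correlation below about 0.43, which the protocol neither gives nor rules out. Nor is the interaction always less efficient than the raw follow-up comparison, since above about 0.43 it is more efficient. Silence about the contrast is not in itself an error.

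The reply does not remove the loss from the free baseline term. That term is in the stated model, and on the reading most favourable to the protocol power at r = 0.5 is still 84.5% rather than 90.0%. It is also fair to say that changing a primary model after recruitment has begun is more than an edit to wording.

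**Conclusion.** The point holds as one of efficiency and clarity. Under either reading, the stated model is less precise than one with a common baseline mean for any r strictly between 0 and 1. At r = 0.3 the power is 73.3% (interaction) or 81.7% (follow-up contrast) against 83.7%. At r = 0.5 it is 84.5% on both readings against 90.0%. A shortfall from the stated 80% arises only if the interaction is the test and r is under about 0.43. It is possible, not demonstrated.

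The sizes rest on the assumptions listed with the inputs, above all equal SDs, 55% follow-up in each arm and missingness at random. They apply to the continuous outcomes only, not to the logistic mixed models for attempts to change.

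**What to change.** For the continuous outcomes, code time as 0 at baseline and 1 at follow-up and drop the group main effect, so that both arms share one baseline mean (a constrained longitudinal model). Keep all participants with baseline data, as already planned. The group by time coefficient is then the group difference at follow-up. Name it as the primary contrast, and state that the differences in Sample size and power refer to it.

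ANCOVA of follow-up on arm plus baseline has the same precision, but it includes only participants with follow-up data (about 372 of 675) and so departs from the planned analysis set. The constrained model is the closer fit.

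Power is then at least the stated 80% (to rounding) at any correlation. No new data or participants are needed. The cost is an amendment: the Protocol amendments section requires ethics approval, a registry update and disclosure in the outcome publication. Recruitment began in October 2019, so the change should be dated and justified from the design alone, without reference to outcome data.
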